### Process Evaluation

The relevance, applicability, and feasibility of our education toolkit will be assessed using qualitative research methods. In the intervention arm, we will purposively identify and recruit relevant toolkit end users, including the health educators and participants of the Transform Program. We will purposively select 30 stakeholders to participate in semistructured interviews within 2 weeks after the end of the Transform Program as in Multimedia Appendix 1. The interview will aim to understand the accuracy and appropriateness of the toolkit content, user perceptions of the relevance of the toolkit, and overall satisfaction with the toolkit.

Interviews will be conducted in person, online, or by phone, depending on the availability and preference of interviewees, by members of the Canadian research team or research staff from ICM. Interviews will be conducted in the preferred language of the interviewee. In cases where interviews are not conducted in English, an interpreter will be hired to assist with interview facilitation. Each interview will begin with an explanation of the study, followed by the delivery of a verbal consent script and signing of the consent document. Consent will be obtained for both study participation and audio recording (the consent process is described in detail in the subsequent section). Each interview is expected to last 40 to 60 minutes with the aid of an interview guide. Interviews will be audio recorded. For participants who consent to study participation but not to audio recording, we will seek consent to take notes during the conversation. Data collected from the interviews will be transcribed from the recordings. We will use a thematic analysis approach following the 6-phase framework of Braun and Clarke: (1) data familiarization through repeated reading of transcripts and noting initial ideas, (2) systematic coding of meaningful features across the dataset, (3) collating codes into initial themes and subthemes, (4) reviewing and refining themes against coded data and the entire dataset, (5) defining and naming themes to capture their essence, and (6) producing the final analytic report [28]. Transcripts will be coded inductively by 2 researchers, with discrepancies discussed and resolved through consensus. The analysis will be performed using NVivo (Lumivero). Throughout the analysis, we will maintain reflexive memos to document assumptions, positionality, and decision-making throughout the analytic process, ensuring transparency and minimizing bias [29]. To strengthen transferability, we will provide descriptions of the study setting, participant characteristics, and contextual factors, enabling readers to assess the applicability of the findings to other contexts [29].

### Ethical Considerations

Ethics approval for this trial was obtained from the Office of Research Ethics at the University of Toronto, Canada (45722) and the ethics committee of ICM (2024-001). Informed consent will be obtained from participants before trial enrollment. The data will be deidentified before analysis. No compensation will be provided to participants.

### Trial Management

The trial will be co-led by XW (University of Toronto) and LL (ICM, Philippines), who will have full access to the trial dataset. To protect the safety and privacy of participants and to ensure that data are collected ethically, stored correctly, and used solely for research, we will establish a data management committee that will be led by external and independent members. In addition, we will form a trial steering committee to oversee the trial design and implementation. Teleconference meetings will be held for both the data management committee and the trial steering committee at the start and midpoint of the study, with the option of additional meetings as necessary. Protocol modifications will be discussed during these meetings.

## Results

This study was funded in 2021 and registered at ClinicalTrials.gov (NCT06218368) on January 23, 2024. Participant recruitment was launched on January 31, 2024, and completed on February 29, 2024. A total of 3613 participants have been recruited for the trial. Data collection is ongoing and is expected to be completed by June 30, 2025, and we plan to disseminate the results by September 30, 2025. We will disseminate the trial results through research articles and policy briefs. We aim to publish our results in leading international medical journals and present them at national and international conferences. The total lifespan of the study will be 23 months, as shown in Table 2.

**Table 2 table2:** Study timeline.

			Study period (months)										
			1-3		4		5-8		9-10		11-20		21-23
**Preparation**													
	Study design	✓											
	Development of research tools	✓											
	Ethics evaluation	✓											
**Interventions**													
	Enrollment			✓									
	Intervention arm			✓		✓							
	Control arm			✓		✓							
**Evaluation**													
	Primary outcome data collection			✓		✓		✓		✓			
	Process evaluation data collection			✓		✓		✓		✓			
	Data analysis and results dissemination											✓	

## Discussion

### Anticipated Findings

Our trial aims to assess the effectiveness and feasibility of an education toolkit developed in collaboration with local stakeholders to enhance confidence in measles and polio vaccines among communities living in extreme poverty in the Philippines. Conducted in partnership with ICM, the trial will use a cluster randomized controlled design across 4 bases in the Philippines. Eligible participants from communities participating in the Transform Program of ICM will receive either the intervention, consisting of a 10-minute educational video about the efficacy and safety of measles and polio vaccines and vaccination reminders, or standard program sessions delivering health education through participatory adult learning sessions. Primary outcomes will include measles vaccination rates among the children of the participating families, and secondary outcomes will include polio vaccination rates, participant knowledge, and attitudes toward vaccines. In addition, the feasibility of the intervention will also be assessed.

Our intervention aims to address the last mile challenge of reaching WHO vaccination targets by improving knowledge and awareness of measles and polio vaccines among the communities living in extreme poverty in the Philippines and to complement the continuing efforts of the DOH to improve measles and polio vaccination coverage. By adopting a community-based approach and embedding our intervention within an existing community-based program run by our local partner, we leverage the established trust between community members and health educators. This approach is expected to enhance the acceptability and effectiveness of our intervention, as community members are more likely to engage with familiar and trusted sources of information, namely, pastors and the nongovernmental organization facilitating the program. In addition, using local health educators and staff who have long-standing working relationships with these communities will facilitate cultural competency and help ensure that interventions are tailored to meet the unique needs of the target population. Evidence on the impact of the intervention and the factors influencing its impact will be generated from the trial, and local stakeholders will be informed about the sustainability and scalability of this intervention to other regions of the Philippines. By systematically documenting the outcomes and lessons learned, we seek to contribute valuable insights that can guide the development and implementation of future community-based interventions aimed at improving vaccination coverage and addressing health disparities among marginalized populations.

### Strengths and Limitations

Our trial has the following strengths. First, the use of a cluster randomized controlled design enhances the validity of the study, providing a rigorous framework to evaluate the effectiveness of the intervention. This design will enable us to draw robust conclusions about the impact of the education toolkit on vaccination rates and knowledge. Second, using an implementation science approach will offer valuable insights into the facilitators and barriers encountered during the implementation of the intervention. By understanding the contextual factors influencing the success of the intervention, local stakeholders will be able to make informed decisions about its implementation and sustainability. Finally, this trial leverages our strong ties with our local partners in the Philippines, which strengthens the relevance and impact of our findings. By prioritizing equitable collaboration and engaging local partners from the development phase of the intervention, we aim to ensure that the benefits of the intervention extend to the most vulnerable populations. This approach is expected to foster vaccine confidence and support inclusive vaccination programs that address the needs of all community members.

However, while the vaccination status will be retrieved from the DOH, there is a possibility of missing data on the children of study participants. In such cases, relying on self-reported vaccination status may introduce recall bias, potentially affecting the accuracy of the data. Due to constraints on survey length, only 10 questions related to measles and polio vaccines will be included in the assessment of participants’ knowledge and attitudes. This limited scope may not fully capture the complexity of participants’ beliefs and understanding regarding vaccination. Despite this limitation, careful selection of survey questions based on key indicators will help ensure that essential information is obtained, balancing the depth of inquiry with practical considerations. Second, our intervention will be implemented alongside the soap opera intervention of the Transform Program. If the soap opera intervention is effective, participants in the intervention arm may make greater investments in children’s education, social capital, health, hope, and economic conditions, which would positively impact their children’s vaccination rates. Because the control arms will receive the traditional Transform Program, which includes the same content, any additional effect would be attributable to the soap opera delivery method, which is part of our intervention. Finally, participants in both arms may miss the health education and vaccine sessions due to other commitments, which could reduce their level of engagement with the intervention and its overall effectiveness.

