### Study Design

We will use a pragmatic, parallel, cluster randomized controlled trial to assess the effectiveness of an education toolkit in improving public confidence in measles and polio vaccines in the Philippines.

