### Process

#### Intervention Arm

All participants of the existing trial (ie, 30 participants per community) in the intervention arm will receive a series of 15 soap opera videos, 1 for each week, to complement the 15-week Transform Program’s education sessions, which are the core intervention of the Soap Opera Trial developed and run by ICM. The 15 episodes were designed to be consumed as a series, with the storylines for each character extending throughout the 15 videos. The characters were developed to reflect situations and contexts comparable to those of the audience, increasing the likelihood that they will relate personally to the story and messages. The videos were shown on televisions brought into the communities (ICM also tested projectors, but the screen setup and lighting proved too logistically challenging). Speakers were also brought into each “watch-session,” and a variety of tests were conducted to ensure that the audience would be able to engage properly with the videos. The soap opera is a popular medium in the Philippines and is widely consumed by the target population. According to NGP, a Filipino-based agency, soap operas are important media sources for Filipinos. Given that the eligible participants live in extreme poverty, the soap operas are a strategic medium for health messaging [24,26]. In addition, all participants in the intervention arm will receive our education toolkit intervention from weeks 12 to 15.

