The intervention in our Vaccine Confidence Trial contains two components: (1) education on measles and polio vaccination in the form of a 10-minute video and (2) reminder messages regarding vaccination. The education toolkit will contain information and messages about the following four aspects of measles and polio vaccines: (1) a comprehensive introduction to measles and polio, (2) vaccine safety and efficacy, (3) measles and polio vaccination guidelines and schedules, and (4) myths and misconceptions. In the toolkit, we will provide information on (1) the definitions of measles and polio, (2) the importance of measles and polio prevention, (3) the side effects of the vaccines, and (4) vaccination provision locations. The education toolkit will be presented in local languages using a 10-minute video converted from Microsoft PowerPoint slides. The PowerPoint slide deck and accompanying script were collaboratively developed with health educators from ICM. Professional translators have translated the finalized English version of the slide deck and script into the local languages. Subsequently, ICM produced a video featuring a health worker presenting the toolkit, synchronized with the voiceover and PowerPoint slides.

Following the delivery of the video, participants will also receive reminder messages regarding vaccination from health educators from ICM in the savings groups program running in communities for 4 months. For participants whose children are not yet vaccinated, the health educators will remind them about the importance and benefits of measles and polio vaccination. This process will serve as a reminder for parents about the importance of measles and polio vaccination. In the typical Transform Program, approximately 40% to 50% of participants will self-select to form a savings group, which ICM will support for 2 years. In these groups, participants will receive weekly reminder messages about measles and polio vaccination in their meetings for 4 months.

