#### Control Arm

In the control group, participants will attend the standard 15-week Transform Program, with education sessions delivered through standard participatory adult learning sessions by health educators from ICM on the topics of income creation, education, food security, health, and resilience, with key messages consistent with the soap opera videos. No specific educational information will be provided regarding measles and polio vaccination, and no specific reminders regarding measles and polio vaccinations will be provided.

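### The arm difference measures the soap opera and the vaccine toolkit together, but the protocol states its aim and planned conclusion as the effect of the toolkit alone.

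*Protocol article*

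**What the plan says.** The Study Design section describes a "cluster randomized controlled trial to assess the effectiveness of an education toolkit in improving public confidence in measles and polio vaccines". The Objective in the Abstract and the Objectives section of the Introduction put it the same way. The Statistical Analysis section speaks of the toolkit's effect on the knowledge and attitude scores. The first paragraph of Strengths and Limitations promises firm conclusions about what the toolkit does to vaccination rates and knowledge.

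The Intervention Arm section defines what is tested: "The intervention in our Vaccine Confidence Trial contains two components: (1) education on measles and polio vaccination in the form of a 10-minute video", the second component being reminder messages. The soap opera is not listed. Table 1 also places it in the Soap Opera Trial column and only the video and reminders in the Vaccine Confidence Trial column.

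The same Intervention Arm section says that all participants in that arm "will receive a series of 15 soap opera videos, 1 for each week", with the toolkit added in weeks 12 to 15. Controls attend the standard Transform Program, and "No specific educational information will be provided regarding measles and polio vaccination"; they get no vaccination reminders either. Randomization and Blinding states that the allocation is the one already made for the Soap Opera Trial.

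The second paragraph of Strengths and Limitations says that an effective soap opera would raise children's vaccination rates. It then reasons that controls receive the same content, so that "any additional effect would be attributable to the soap opera delivery method, which is part of our intervention".

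**The concern.** The protocol gives two incompatible accounts of its intervention. In the aim, the definition, Table 1 and the promised conclusion, it is the toolkit. In the limitations paragraph, it includes the soap opera. If the soap opera is part of the intervention, the trial estimates a package effect and the toolkit wording elsewhere is wrong. If it is not, it is a co-intervention given to one arm only, and the toolkit effect is confounded with it.

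At stake is what a positive primary result would mean. The article intends its findings to inform scale-up elsewhere. A reader could conclude that a short video and reminders suffice, when the communities that produced the result also had 15 weeks of drama episodes that, on the authors' own reasoning, might raise vaccination.

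**Working it through.** **1. What each arm receives** (Setting, Intervention Arm, Control Arm, Randomization and Blinding)

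| | Intervention | Control |
|---|---|---|
| Transform Program, 15 weeks | yes | yes |
| Soap opera, 15 episodes | yes | no |
| Vaccine video | yes | no |
| Vaccination reminders | yes | no |

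There is one 1:1 allocation. No community is assigned the soap opera without the toolkit, or the toolkit without the soap opera.

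**2. What the contrast estimates.** Let S = 1 if a community is assigned the soap opera and T = 1 if it is assigned the toolkit. On any scale, write the mean outcome as a + b·S + c·T + d·S·T. Intervention communities have S = T = 1 and controls have S = T = 0, so

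arm difference = (a + b + c + d) − a = b + c + d.

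The toolkit effect is c (without the soap opera) or c + d (on top of it). Since S = T in every community, the columns for S, T and S·T are identical and only their sum can be estimated. The planned adjustment for baseline vaccination, sex, age and province does not alter this. Nor does the subgroup analysis by base, because S = T within each base too. A statistical analysis plan could not supply the missing contrast.

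**3. The plan's own sample size.** Inputs from the Sample Size section: 80% versus 90% coverage, two-sided 5%, 90% power, 5 children per cluster, intracluster correlation 0.12.

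- Design effect: 1 + (5 − 1) × 0.12 = 1.48.
- Per arm before clustering, unpooled variance: (1.960 + 1.282)² × (0.8 × 0.2 + 0.9 × 0.1) / 0.10² = 262.7.
- Clusters per arm: 262.7 × 1.48 / 5 = 77.75, rounded up to 78, so 156 in total.

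This matches the stated figure (the pooled-variance formula gives 79 per arm, 158). With the planned 90 clusters per arm, the effective number is 90 × 5 / 1.48 = 304 per arm and power is about 93%. That power belongs to b + c + d, the package contrast. The sample size is not in dispute.

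**4. Illustration with assumed soap-opera effects.** The documents give no soap-opera effect on first-dose measles coverage, so the range below is an assumption. Take the toolkit effect as exactly zero, control coverage as 80%, and 304 effective children per arm. With p₁ = 0.80, p₂ = 0.80 + Δ, p̄ their mean and Φ the standard normal distribution function, the chance of a significant result favouring the intervention arm is

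Φ{[Δ√304 − 1.96√(2p̄(1 − p̄))] / √[p₁(1 − p₁) + p₂(1 − p₂)]}.

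| Assumed soap-opera gain Δ (points) | Chance of a significant result with no toolkit effect |
|---|---|
| 0 | 2.5% (half of the two-sided 5%) |
| 2 | 9% |
| 3 | 16% |
| 5 | 37% |
| 7 | 64% |
| 10 | 93% |

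The table shows only that the attribution matters if the soap opera works. It does not say that it does.

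**The case against.** The strongest reply is that nothing is hidden. The Abstract, the Setting section, Table 1 and the Intervention Arm section all describe the embedding in the Soap Opera Trial, and the limitations paragraph names the soap opera and gives the direction of its possible effect. Randomisation is sound, and the test answers a well-defined question about the package. All of that stands. Disclosing the co-intervention does not resolve it, however, because the aim and the promised conclusion still refer to the toolkit.

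Three stronger readings are tempting but not supported.

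- A reader might infer that the limitations paragraph contradicts the Control Arm section, since controls cannot have had the same content if they had no vaccine education. In context, the remark most naturally concerns the general Transform messages. The Setting and Control Arm sections do describe those as shared by both arms, so the two sections are compatible.
- A reader might infer that the toolkit effect is overstated, or assign the soap opera a share of the planned 10-point difference. The authors' statement is conditional on the soap opera being effective. Vaccination is not among the health topics that the Setting section lists for the program, and controls hear the same general messages. A zero effect is compatible with the documents.
- A reader might want reminder reach in the estimand, because reminders run through savings groups and "approximately 40% to 50% of participants will self-select to form a savings group". That figure describes the typical program, not this trial. It concerns uptake, which an intention-to-treat comparison absorbs, and has no bearing on separating the soap opera from the toolkit.

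**Conclusion.** The concern holds as a matter of attribution. The trial can estimate the effect of the soap-opera Transform Program plus vaccine video plus reminders against the standard Transform Program. It cannot estimate the effect of the toolkit. The toolkit-only statements in the Abstract, Objectives, Study Design, Statistical Analysis and Strengths and Limitations therefore go beyond the design, and the limitations sentence conflicts with the two-component definition and with Table 1.

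This conclusion rests only on the allocation as described and needs no assumed effect. The size of any misattribution cannot be derived from the documents and may be nil. The randomised comparison, the test and the planned power stand for the package.

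**What to change.** 1. In the Abstract, Objectives, Study Design and Statistical Analysis, state the objective and primary estimand as the effect of the combined package (soap-opera Transform Program, vaccine video and reminders) versus the standard Transform Program. Use the same wording for the planned conclusion.
2. Reword the limitations sentence to say that the soap opera is part of the randomised contrast and that the toolkit-specific effect is not identifiable. Describe the intervention consistently with this in the Intervention Arm section and Table 1.
3. Remove the promise of conclusions about the toolkit alone from the first paragraph of Strengths and Limitations.

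Recruitment closed on February 29, 2024, so no new arm is proposed. Showing the Soap Opera Trial's non-vaccine outcomes beside the vaccine result could be useful description if that trial's team agrees, but it would not separate the components and is optional.

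The cost is editing and a less specific claim. Data collection, the model and the primary test do not change.
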